## 8.2 Control

Participants allocated to the control group will undergo the same timing and assessments of follow-up visits without postoperative knee injection. Participants in both groups should avoid co-interventions which may cause confounding biases, including unscheduled knee injection and non-steroidal anti-inflammatory drugs, while acetaminophen can be prescribed for participants who report a moderate to severe pain if required (should be suspended for 7 days before clinical assessments). If participants receive additional medications or treatment out of the protocol, they should report them completely to the clinicians at follow-up visits.

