## **Section 11. Adverse Events**

### **11.1 Definition and Classification**

Adverse event (AE) refers to any unfavorable and unintended sign (including an abnormal laboratory finding), symptom, or disease temporally associated with the use of a medical treatment or procedure in a patient or clinical investigation subject, whether or not related to the medical treatment or procedure. AEs are usually graded by the severity:

- ① Mild AEs: asymptomatic or mild symptoms; observations only; intervention not indicated.
- ② Moderate AEs: minimal or local intervention indicated; limiting instrumental activities.
- ③ Serious AEs (SAEs): AEs that (1) results in death, (2) is life-threatening, (3) requires inpatient hospitalization or causes prolongation of existing hospitalization, (4) results in persistent or significant disability, (5) may have caused a congenital anomaly or birth defect, or (6) requires intervention to prevent permanent impairment or damage.

In this study, the AEs are classified into intervention-related AEs (only occurrence in intervention group and probably related to the intervention) and common AEs (occurrence in both groups, whether or not increased with intervention). Possible intervention-related AEs include fainting, allergic reaction, pain at injection site, knee swelling, decreased range of motion, and infection at injection site. Because of the study population (patients with ACL injuries and undergoing ACLR), common AEs should include all complications and unfavorable outcomes accompanied with ACL injuries as well as those with ACLR, such as graft failure, residual laxity, decreased range of motion, and arthrofibrosis.

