## **Section 12. Statistical Analysis**

### **12.1 Primary Analysis**

The primary analysis will be performed following the intention-to-treat principle, which emphasizes on the original group allocation by randomization. Specifically, once a participant is enrolled and undergoes randomization, the baseline and outcome measures will be included in the allocated group, regardless of whether the participant violates the protocols and whether the participant is dropout during follow-up: (1) if a participant is randomized to the intervention group but does not receive 3 doses of PRP injection, this participant will not be

excluded from the intervention group; (2) if a participant is randomized to the control group but receives knee injection out of the protocol, this participant will not be excluded from the control group; (3) if a participant is randomized to either group but lost to follow-up, this participant will not be excluded from the primary analysis, either. In principle, the primary analysis should include all participants randomized in this study. For the missing data, simple or multiple imputation will not be performed in the primary analysis.

All statistical analyses will be performed using the IBM SPSS software, with a 2-sided significance level of 0.05. Descriptive statistics will be presented as mean and SD (for normally distributed values), median and interquartile range (for non-normally distributed values), or number and percentage (for categorical variables).

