#### ① Subjective assessments

The primary outcome, KOOS4 at 12 months, has been validated to be associated with knee symptoms and pain at baseline. Referenced to statistical methods in previous studies, an analysis of covariance (ANCOVA) will be performed to analyze the between-group difference using the baseline KOOS4 as the covariate for adjustment. For other subjective assessments included in the secondary outcomes, ANCOVA models will also be applied to analyze the between-group differences with adjustment for the corresponding baseline scores. Between group differences will be presented as mean, 95% confidence interval (CI), and P value. For an outcome with a statistically significant difference, the clinical significance should be evaluated by comparing the mean and 95% CI with the MCID.

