#### ③ Other variables

The Kolmogorov-Smirnov test will be applied to evaluate the normality for continuous variables. The Student t test will be used for comparison of continuous variables with normal distribution. The Mann-Whitney-Wilcoxon test will be used for comparison of non-normally distributed continuous variables and ordinal variables (including GROC, amount of ACL

remnant, and grades of knee laxity). The Pearson chi-square test or Fisher exact test will be used for comparison of categorical variables (including demographic data and adverse events), depending on expected frequencies for the contingency tables.

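### Adverse events are assigned a chi-square or Fisher test with no effect estimate or interval, including injection-site events that the control group cannot have

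*Protocol*

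**What the plan says.** Section 12.1 ③ (Other variables) fixes the method: "The Pearson chi-square test or Fisher exact test will be used for comparison of categorical variables (including demographic data and adverse events"), the choice between the two depending on expected frequencies. Section 12.1 applies one threshold to everything: "All statistical analyses will be performed using the IBM SPSS software, with a 2-sided significance level of 0.05". Categorical variables are also summarised as "number and percentage (for categorical variables").

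An effect estimate with an interval is specified in Section 12.1 ① only, for the subjective scores: "Between group differences will be presented as mean, 95% confidence interval (CI), and P value". No counterpart is given for adverse events.

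Section 11.1 divides adverse events into two classes. One is "intervention-related AEs (only occurrence in intervention group and probably related to the intervention"); the other is common events, seen in both groups. For the first class it says: "Possible intervention-related AEs include fainting, allergic reaction, pain at injection site, knee swelling, decreased range of motion, and infection at injection site". Section 8.2 describes the comparator: "Participants allocated to the control group will undergo the same timing and assessments of follow-up visits without postoperative knee injection". Section 7.2 adds that, in the single-blind design adopted, only the intervention group has blood drawn.

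**The concern.** The definition of adverse events and their analysis do not fit together. Section 11.1 sets up a class that occurs in one group only, and Section 12.1 ③ then sends all adverse events to a between-group test without excepting that class. If controls have no injection, their risk of pain or infection at an injection site is zero by design. A test of equal risk then answers no question of interest, and a non-significant P value can sit beside several events that the injections caused.

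For events that both groups can have, the question is real. But the trial was sized for KOOS4, and a P value alone does not show how large an excess remains compatible with the data. The trial adds three intra-articular injections to routine recovery. Section 12.1 ① judges benefit by setting the estimate and its interval against the MCID, whereas harm gets no interval. What is at stake is whether the safety statement can say what rate of harm the data exclude.

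**Working it through.** **Inputs.** 60 per group, or 51 before the dropout allowance (Section 5); two-sided 0.05 (Section 12.1); Pearson or Fisher by expected frequencies (Section 12.1 ③); no injection in controls (Section 8.2). The protocol gives no adverse-event rates, so the rates below are assumptions shown over a range. It gives no cut-off for expected frequencies either. I assume Fisher when any expected count is below 5, and Pearson without continuity correction otherwise.

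**The plan's own figure.** Effect size 13/20 = 0.65. With the noncentral t distribution, power is 0.896 at 50 and 0.902 at 51 per group; 51/0.85 = 60 per group, 120 in total. The sample size reproduces. It concerns KOOS4; no power is stated for adverse events.

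**Events that controls cannot have.** With k events among 60 against 0 among 60, the two-sided Fisher value is P = 2 × C(60,k)/C(120,k):

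- k = 3: 0.244
- k = 4: 0.119
- k = 5: 2 × 5,461,512/190,578,024 = 0.057
- k = 6: 0.027

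So 6 events are needed; the same minimum holds at 51 per group. Since the control count is always 0, power is the probability that a Binomial(n, p) count is at least 6:

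| True PRP rate | Power, 60 per group | Power, 51 per group |
|---|---|---|
| 5% | 8% | 4% |
| 8% | 35% | 22% |
| 10% | 56% | 40% |
| 15% | 90% | 80% |
| 20% | 99% | 96% |

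Exact (Clopper-Pearson) 95% intervals for the PRP group: 5/60 = 8.3%, 2.8% to 18.4%; 3/60 = 5.0%, 1.0% to 13.9%; 0/60, upper limit 1 − 0.025^(1/60) = 6.0%.

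**Events possible in both groups.** All 2×2 tables were enumerated, the test rule above was applied to each, and the binomial probabilities of the tables with P ≤ 0.05 were summed:

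| Control vs PRP | Power, 60 per group | Power, 51 per group |
|---|---|---|
| 5% vs 10% | 14% | 10% |
| 5% vs 15% | 44% | 35% |
| 5% vs 20% | 72% | 64% |
| 10% vs 20% | 33% | 28% |
| 10% vs 30% | 80% | 73% |

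**What an interval would add.** Take 9/60 against 3/60. The expected event count is 6 per group, so Pearson applies: χ² = 120 × (9×57 − 3×51)²/(60×60×12×108) = 3.33, P = 0.068. The risk difference is 15% − 5% = 10 points, Newcombe 95% CI −1.1 to 21.6. The P value alone reads as non-significant. The interval shows that an excess above 20 points is not excluded.

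**The case against.** A good deal can be said for the plan.

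- **The P value is not the only safety information.** Counts and percentages are planned (Section 12.1), and the timing, course, outcome and relation to the intervention of each event are recorded (Section 11.2). The IRB receives a complete adverse-event analysis (Section 13). The proposed intervals could be computed from the published counts.
- **Some harms are also measured as outcomes.** Range of motion and knee circumference are recorded at every follow-up (Section 10.4) and compared between groups. For motion and swelling the binary test is therefore not the only comparison. This does not cover infection, fainting, allergic reaction or graft failure.
- **Common reactions would be seen.** A reader might infer that the test would usually miss a harm of PRP. That depends on the rate: at 15% against none, power is 90%.
- **No rule equates non-significance with safety.** A reader might infer that the investigators will conclude there is no harm from P > 0.05. The protocol nowhere says so, and its stated purposes (Section 2) are efficacy outcomes.
- **Low power comes from the trial's size.** An interval displays the imprecision and does not cure it.
- **Table layout and interval method are often left to a separate plan.** That would answer a complaint about omission. Here the document, titled as both protocol and analysis plan, states a method, and that method does not suit one of its own event classes.

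These points limit the concern to how adverse events are analysed and reported. They do not remove the mismatch between Sections 11.1 and 12.1 ③.

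**Conclusion.** The point holds as a weakness in the specified analysis of adverse events. For injection-site events the between-group test is void by design, and 5/60 against none would still be labelled non-significant. At 60 per group, a true rate below roughly 9% to 10% against none is missed more often than not. So is an excess of 10 points or less over a 5% to 10% background. Harms of 15% or more against none are usually detected.

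These sizes rest on assumed event rates and on the assumed cut-off of 5 for expected counts. The statement that the test has no meaning for injection-site events rests on neither.

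Nor should every event that Section 11.1 lists as possibly intervention-related be taken as impossible in controls. Swelling and reduced motion can occur in both groups, and reduced motion appears in both of that section's lists. The primary analysis and the sample size are unaffected.

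**What to change.** In Section 12.1 ③, take adverse events out of the chi-square/Fisher sentence and add three rules:

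1. Events possible in both groups: number and percentage per group, with a risk difference and 95% CI (for example Newcombe).
2. Events that require the blood draw or the injection, such as pain or infection at the injection site: number and percentage of participants in the PRP group, with an exact (Clopper-Pearson) 95% CI and no between-group test.
3. The safety statement cites the interval, in particular its upper limit; P > 0.05 is not taken as evidence of safety.

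Assign events to rule 1 or rule 2 by whether a control participant could have them, and list the assignment in advance, because the classes in Section 11.1 overlap.

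The cost is a change of wording and one table, from data already collected. The drawback is that wide intervals will be visible and the safety statement will look less favourable.

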## **12.2 Post-hoc Sensitivity Analyses**

For all outcomes with missing data, the number, proportion, and reasons of patients who are not available for the outcome should be reported. For any outcome with missing data >5%, multiple imputation by chained equations (fully conditional specifications method) should be performed with 20 iterations to evaluate the bias caused by non-random missing and detect any change towards a different direction of the significance level. Variables in the imputation model should include group allocation, age, gender, sports participation, graft diameters, meniscal treatment, and baseline KOOS4 (or corresponding baseline evaluation, if applicable). These variables are potential predictors and confounders of clinical outcomes and may also be explored in multivariate linear regression analyses to quantitatively compare the effects of different factors associated with the clinical outcomes.

Furthermore, per-protocol (as-treated) analyses for all outcomes should be performed based on the criteria of protocol violation. In this context, participants who receive reoperation or any unscheduled knee injection (more, less, or violation of injection schedules) should be excluded from the originally randomized group. In particular, if a participant is found out to receive the intervention or control following exactly the same protocol as the opposite group, this participant should be included in the opposite group. Per-protocol analyses will follow the above-mentioned statistical methods in the primary analysis.

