### **Section 5. Sample Size**

The minimal clinically important difference (MCID) of the primary outcome varies among studies, ranging from 8 to 40 for each subscale among patients with knee injuries or osteoarthritis. Based on the anchor-based method, the MCIDs are 10.7–16.7 for the 4 subscales, averaged 13.8. Therefore, the statistical hypothesis is based on detecting a between-group difference of 13 points. The maximum SD is estimated to be 20 points, thus the effect size is 0.65. With the 2-sided significance level and power setting at 0.05 and 0.9, respectively, a sample size of 51 participants is required in each group (1:1 allocation, calculated using G\*Power 3.1, based on the test of mean difference between two independent groups, and assuming a balanced baseline). After adding the dropout (estimated within 15%), a total of 120 participants (60 in each group) should be included in this study.

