## Section 10. Outcome Measures

### 10.1 Primary Outcome

The primary outcome of this study is the KOOS4 score at 12 months postoperatively. The KOOS has been developed for evaluating knee symptoms and function in a variety of knee injuries and osteoarthritis and validated in ACL-injured and ACL-reconstructed patients. KOOS includes 42 items covering 5 subscales: pain (9 items), symptoms (7 items), function in activities of daily living (17 items), function in sports and recreation (5 items), and quality of life (4 items). For each item, the responses are presented in 5-point Likert scales (range, 0–4). For each subscale, the overall scores are summed by each item and standardized to range from 0 to 100, with higher scores indicating fewer symptoms or better knee function (100 indicating best knee function without symptoms). Given that patients with ACL injuries and ACLR have relatively high scores of the function in activities of daily living subscale, some high-level studies have introduced KOOS4, which is calculated as the average score of the other 4 subscales (pain, symptoms, function in sports and recreation, and quality of life), to avoid the ceiling effect. Based on the anchor-based MCIDs for each subscale of the KOOS, the MCID for KOOS4 is determined as 13 points in this study.

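### The planned multiple imputation assumes missing at random, so it cannot evaluate bias from non-random missingness, and for the primary outcome it nearly repeats the complete-case ANCOVA

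*Protocol*

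**What the plan says.** Section 10.1 fixes the endpoint: "The primary outcome of this study is the KOOS 4 score at 12 months postoperatively". Section 12.1 analyses it by ANCOVA with baseline KOOS4 as covariate and rules out imputation in the primary analysis, so that analysis rests on completers.

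Section 12.2 holds the only sensitivity analysis for missing data. Above 5% missing, "multiple imputation by chained equations (fully conditional specifications method) should be performed with 20 iterations". Its aim is "to evaluate the bias caused by non-random missing and detect any change towards a different direction of the significance level". On predictors it says: "Variables in the imputation model should include group allocation, age, gender, sports participation, graft diameters, meniscal treatment, and baseline" KOOS4, or the corresponding baseline measure for other outcomes. The section also asks for the number, proportion and reasons of missing data. Its per-protocol analysis deals with protocol violations, not with missing values.

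Two other places bear on this. Section 10.2 collects the KOOS subscales at 3, 6 and 12 months, so KOOS4 can be computed at 3 and 6 months. Section 7.2 leaves participants aware of their allocation.

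**The concern.** The stated purpose and the stated method do not fit together. Standard fully conditional specification draws each missing value from relationships seen among participants with data. It therefore assumes that, given the predictors, those who are missing resemble those who are observed. Non-random missingness is the failure of exactly that assumption. Agreement between the imputed and complete-case results is no evidence against it.

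For the primary outcome there is a second problem. The ANCOVA already conditions on arm and baseline KOOS4, and the imputation list adds only other baseline and surgical variables, so the two analyses use almost the same information. A reader who takes section 12.2 at its word could read their agreement as robustness to non-random dropout, which was never tested.

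The loss must be outcome-related and differ between arms to bias the comparison. That is plausible here: participants know their arm, the primary outcome is self-reported, and only the PRP arm attends for blood draws and injections.

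**Working it through.** **1. The plan's own figures.** Section 5 gives: "the statistical hypothesis is based on detecting a between-group difference of 13 points"; "The maximum SD is estimated to be 20 points"; "With the 2-sided significance level and power setting at 0.05 and 0.9, respectively, a sample size of 51 participants is required in each group".

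- Normal approximation: n = 2 × (1.960 + 1.282)² × 20² / 13² ≈ 49.7, so 50 per group.
- Exact noncentral-t power is 0.896 at 50 and 0.902 at 51, so 51 is reproduced.
- With 15% dropout, 51 / 0.85 = 60 per group, 120 in total. This is also reproduced, and the sample size is not at issue.

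**2. Does the imputation add to the ANCOVA?** This was simulated with 120 participants, SD 20, 15% missing per arm, true effect zero and 800 replicates per scenario. Imputation used 20 Bayesian linear-regression draws from allocation, baseline score and five further baseline variables. That is what chained equations reduce to when only the outcome is incomplete. The protocol gives no correlations, covariate effects or missingness mechanisms. All are assumptions, and the mechanisms are deliberately strong.

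| Mechanism of loss | Baseline correlation | Complete-case bias | Imputation bias |
|---|---|---|---|
| Low scorers lost in PRP, high scorers lost in control | 0.2 / 0.4 / 0.6 | 6.8 / 5.9 / 4.8 | 6.5 / 5.6 / 4.5 |
| Outcome-related loss in PRP only | 0.2 / 0.4 / 0.6 | 3.4 / 3.0 / 2.3 | 3.2 / 2.8 / 2.2 |
| Same outcome-related loss in both arms | 0.2 / 0.4 / 0.6 | at most 0.25 | at most 0.25 |
| Loss depends on baseline score only | 0.2 / 0.4 / 0.6 | about 0 | about 0 |

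- Across these null scenarios the two estimates correlated 0.98–0.99, differed on average by about 0.4–0.5 points, and agreed on significance in 94–99% of replicates.
- In the first mechanism at correlation 0.4, the false-positive rate was 41% complete-case and 35% after imputation.
- Giving the extra covariates more strength (about 11% of outcome variance) under that mechanism gave bias 5.8 against 5.0, correlation 0.98, agreement on significance 91%, and false-positive rates of 39% and 30%.
- Adding a 6-month score (assumed correlation 0.7 with the 12-month score) cut the imputation bias from 5.6 to 3.4. It helps but does not remove the bias, because the analysis still assumes missing at random.

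**3. What a departure from missing at random would do.** If missing PRP participants score δ below their imputed values, the PRP mean, and so the difference, falls by (missing fraction) × δ. With 15% missing this is 9/60 × δ: 1.5 points for δ = 10 and 3.0 for δ = 20.

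- SE = 20 × √(2/51) = 3.96.
- Smallest significant difference = 1.984 × 3.96 = 7.86 (t, 100 df).
- Tipping shift = (observed difference − 7.86) / 0.15.

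| Observed difference | Calculation | Tipping shift |
|---|---|---|
| 13 | (13 − 7.86) / 0.15 | about 34 points |
| 10 | (10 − 7.86) / 0.15 | about 14 points |
| 9 | (9 − 7.86) / 0.15 | about 8 points |

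This uses the unadjusted SE at the protocol's maximum SD and holds it fixed. Baseline adjustment multiplies the SE by about √(1 − ρ²). For assumed ρ = 0.2 / 0.4 / 0.6 the smallest significant difference becomes about 7.7 / 7.2 / 6.3. The tipping shift becomes about 15 / 19 / 25 points for an observed 10, and about 9 / 12 / 18 for an observed 9.

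**The case against.** **The wording may be loose.** Non-random may mean only not completely at random, which this method can address. That reading is possible. It removes the contradiction in wording, but for the primary outcome the check remains nearly redundant.

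**The predictor list is a minimum.** It does not forbid adding the 3- and 6-month scores. True, so their absence is a weakness to repair, not an error. With them the analysis would still assume missing at random.

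**A separate analysis plan could add more.** It could. The point does not rest on an omission: section 12.2 itself names the method, the predictors and a purpose that the method cannot serve.

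**The practical effect may be small.** Equal outcome-related loss in both arms gives almost no bias. A result at the 13-point design difference would need a shift of about 34 points to lose significance. Differences of 9 or 10 lie below the protocol's MCID of 13, and section 12.1 already requires comparison with it. Reported reasons for missing data also help. All of this stands and limits the size of the concern.

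**Stronger readings that the documents do not support.** A reader might infer that the imputation returns the ANCOVA estimate exactly. It does not, since the list also holds age, gender, sports participation, graft diameters and meniscal treatment. A reader might extend the redundancy to every outcome. SNQ, range of motion and circumference are compared without baseline adjustment, so imputing from baseline values can add information there. A reader might also take the 20 iterations as a definite error. They may simply mean 20 imputed datasets, so this is a clarification only.

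**Conclusion.** The point holds in this form: the imputation in section 12.2 is a missing-at-random analysis and cannot evaluate bias from non-random missingness. For 12-month KOOS4 it also nearly repeats the complete-case ANCOVA.

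The mismatch between purpose and method follows from the text and needs no simulation. The size is conditional. Bias requires outcome-related loss that differs between arms, which the open allocation makes plausible but does not establish. The simulated biases rest on assumed correlations and strong mechanisms, and the tipping shifts on SD 20, 51 completers per arm, 15% missing in the PRP arm and a fixed unadjusted SE. On those terms a result at the design difference is robust, while one nearer the significance boundary may not be. The primary estimate and the sample size are unaffected. What lacks support is a claim of robustness to non-random dropout. This should be changed before analysis.

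**What to change.** In section 12.2:

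1. Describe the chained-equations imputation as an analysis under missing at random, and drop the claim that it evaluates non-random missingness.
2. Add the 3- and 6-month values of the same outcome, where collected, to the imputation model.
3. Prespecify for 12-month KOOS4 a delta-adjusted tipping-point analysis: shift the imputed values in steps, separately by arm (for example 0 to 20 points or more), and report the shift at which the conclusion changes. A range ending at 20 would not reach the tipping point for an observed difference of 13 in the illustration above.
4. As a minor clarification, state the number of imputed datasets separately from the number of iterations.

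The cost is a few sentences and a little extra analysis time. No new data, visits or participants are needed.
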